## Abstract

**Background:**

Child psychological distress in refugee settings is a significant public health concern, which is exacerbated by poor caregiver mental health and functioning. However, there are limited studies about effective interventions to improve caregiver mental health in support of child wellbeing. The objective of the current study is to evaluate the effectiveness and implementation of the Journey of Life (JoL) intervention to improve caregiver mental health in a refugee camp in Western Uganda.

**Methods:**

A waitlist-control quasi-experimental design is being implemented in the Kiryandongo refugee settlement (intervention *n* = 600, control *n* = 600). Caregiver mental distress, measured using the Kessler-6, was selected as the primary outcome. Secondary outcomes include (a) functioning measured by the World Health Organization Disability Assessment Schedule, (b) social support measured by the Medical Outcomes Study Social Support Survey, and (c) caregiving behaviors according to the Parental Acceptance and Rejection Questionnaire and the Child Protection Index. The study aims to examine the implementation of the JoL intervention through qualitative assessments of intervention feasibility, adaptations, and reach.

**Discussion:**

This trial will add much-needed evidence for the implementation of caregiver psychosocial programming within the humanitarian community. Findings will be disseminated amongst local, regional, and global actors in order to guide potential scale up within humanitarian settings.

**Trial registration:**

Clinical Trials NCT04817098 (Registered: 3/24/21).

## Background

Uganda hosts 1.4 million refugees, approximately two thirds of whom are from South Sudan, and over half of whom are children [1]. Displaced children are vulnerable to the impacts of caregiver wellbeing and parenting practices. Refugee caregivers (including biological parents and legal/custodial guardians) cope with a range of stressors including pre-migration conflict and loss as well as post-migration stressors such as poverty, inadequate or unsafe housing, restrictions on employment, limited access to healthcare and education, and loss of social support networks [2–4]. It is well documented that chronic stress leads to negative coping mechanisms such as alcohol and drug abuse, gender based violence, self-harm behaviors, school absenteeism, and worsening mental disorders among adults [5]. Furthermore, caregiver depression is correlated with increased symptoms of depression among their children [6]. High stress also depletes the ability of caregivers to cope and support their children, leading to compromised caregiving, including unresponsive, overprotective, and harsh caregiving [7]. Living in refugee camp settings can strain caregiver wellbeing and parenting behaviors, which in turn can create barriers to healthy child development.

For children, displacement has been shown to amplify susceptibility to malnutrition, infectious disease, prolonged periods out of school, and vulnerability to transactional sex for income and safety [8, 9]. The stressors experienced by children are further exacerbated when adult support mechanisms are strained [10]. Chronically or highly stressed caregivers are more likely to have children with insecure attachments, which has been shown to pose a risk for subsequent difficulties in children’s interpersonal relationships, self-regulation, and achievement [11]. The relationships between caregiver stress, compromised caregiving, and detriments to child wellbeing have been well documented in studies of diverse refugee communities [6, 12–14].

There is growing evidence that psychosocial interventions supporting caregivers can also improve caregiving abilities. Programming that prioritizes caregiving knowledge and skills have been shown to contribute to improved parenting and child outcomes, such as a warmer parenting style, strengthened relationships, and improved academic achievement for children [15–19]. Additionally, psychosocial support interventions with caregivers have demonstrated success in reducing symptoms of caregiver emotional distress, and have shown improvement in overall caregiver well-being [20–28]. However, approaches that build caregiver capacity and support psychosocial well-being have been underutilized and understudied for their effectiveness in humanitarian settings.

Relatedly, the majority of implementation science studies, which assess the uptake of evidence based practices (EBPs) such as caregiver interventions, are based in high income countries [12]. Building the evidence for the implementation of psychosocial EBPs in humanitarian contexts requires the analysis of ecological, institutional, and interpersonal factors including funding and human resource constraints, security and logistics, and a limited capacity of program staff to rigorously assess factors influencing implementation in addition to overall effectiveness [29, 30]. However, a careful investigation into factors that influence implementation in a humanitarian setting is vital to continued uptake of EBPs, scale-up, and dissemination [31–34].

The primary goal of this study is to evaluate the effectiveness and implementation of the Journey of Life (JoL), an intervention to improve child wellbeing through improved caregiver mental health and psychosocial support (MHPSS), in a refugee settlement in Uganda. Through the evaluation, we will:
Evaluate the impact of JoL on MHPSS outcomes, including the mental health (primary outcome) of caregivers, along with changes in caregiver functioning, social support, and parenting behaviors (secondary outcomes); andInvestigate the implementation of the JoL intervention in terms of feasibility, reach, and adaptations.

## Methods

### Setting

Uganda is one of the most welcoming countries to refugees in the world, with freedom of movement, the right to employment, education, and health. Despite access to these opportunities, 80% of refugees live below the poverty line [35]. Kiryandongo Settlement, the location for this study, has a population of approximately 313,800 people, of whom 17% are refugees; the rest are Ugandan nationals, including internally displaced persons (IDPs). The large majority (99%) of the refugee population in Kiryandongo have fled conflict in South Sudan, while the rest are from the Democratic Republic of Congo, Sudan, Kenya, Burundi, and Rwanda [36]. Approximately 62% of the Kiryandongo population is under the age of 18. In February 2020 there were 847 children identified as unaccompanied, separated, or currently at risk [36]. These numbers are not exhaustive due to incomplete birth registrations and record keeping. Children and adolescents within Kiryandongo consistently report high levels of distress, with 30 to 50% meeting criteria for anxiety and depression [6, 37]. Additionally, 77% of refugees in Kiryandongo reported that when a family member was in psychological distress they were not able to access psychosocial care [38].

### Intervention design

JoL was developed to raise awareness among adults about the psychosocial needs of vulnerable children [39–41]. It provides an opportunity for individuals impacted by conflict and displacement to examine the ways they support children and families in their communities. This JoL adaption focuses on engaging caregivers in building awareness around child protection and fosters psychosocial support through reflection, dialogue, and action. The series of workshops are divided into twelve sessions that include; psychoeducation, self-care, positive parenting, understanding children’s needs, identifying children who need help, and building on children’s strengths. The manualized protocol for 12 sessions is designed to be implemented by non-specialized humanitarian workers. There is an overall emphasis across the curriculum on creating nurturing and caring communities.

### Study design

The proposed study will evaluate the effectiveness and implementation of the JoL intervention using a quasi-experimental waitlist control design. In order to reduce contamination, the treatment group will be conducted in one Ranch (a demarcated segment of the settlement) of Kiryandongo, while the wait-list control group will be in a Ranch that is geographically separate. Participants in the intervention group will receive the program weekly for 12 weeks. The waitlist control group will be invited to participate in the intervention shortly after the endline assessment in the intervention group has been completed (see Fig. 1). Effectiveness indicators will be assessed at baseline and endline.

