### Quantitative study design

Every community member (intervention and wait-list control) invited to participate in JoL will also be invited to participate in the evaluation study. To ensure sufficient power, we conducted a sample size calculation for our primary outcome measure – mental distress, measured through the Kessler 6. The proposed sample size (*n* = 960; assuming 80% retention of an initial *n* = 1200) is adequate for detecting an effect size of 11% with 80% power. R (base library, command power.prop.test) was used to conduct the power analysis. We intend to maximize our sample in order to be able to explore potential differences between males and females, and also to be able to look at per-protocol (those who attend > 75% of sessions) versus intent-to-treat analyses.

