### Data analysis

#### Quantitative analysis

The analytic plan is designed to assess effectiveness of the JoL intervention on MHPSS and caregiving behaviors. The level of significance for all analyses will be set at 5%. We will initially assess the sample in terms of baseline characteristics. Other preliminary data analyses will include studies of patterns of missing data, dropout rates, distributional properties of dependent and other measures, and correlations among outcomes. We will determine if effectiveness differs meaningfully in the intervention group compared to the control group. As the primary intervention is community based, an individual’s specific exposure to intervention activities (e.g. intervention dose received) will not be explored, but rather all individuals within the intervention group will be categorized as intervention respondents and all individuals within the control group will be categorized as control respondents. We will also assess the effect of potential mediators in the causal pathway between treatment and outcome. To explore if efficacy differs by baseline characteristics (moderation), we will model the outcomes with the relevant baseline characteristics and their interaction as predictors. Factor-stratified models (e.g. by gender) may be explored if interaction terms are found to be statistically significant. Our modeling approach to assess changes in outcomes over time will use generalized mixed models for longitudinal data. This class of models does not assume that subjects are measured at all time-points, and therefore can include subjects with two measurement time-points. In these analyses, we will examine changes across time in order to assess – and isolate from programmatic efficacy - the effect of time. Based on intervention attendance records, both intention-to-treat and per-protocol analyses will be explored. We will also conduct sensitivity analyses to investigate the robustness of results across different models for missing data, following this detailed approach. Additional analyses will also be explored, such as the need for models that use inverse probability weighting to account for potentially high levels of incomplete intervention participation within the intervention community.

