#### Dissemination

The results of this project will be disseminated internally among implementation staf of TPO and REPSSI about the use and implementation of JoL. Results will be shared in verbal and written formats to ensure accessibility. Additionally, presentations about outcomes will be organized for UNHCR agency meetings both in settlement locations and among agencies in Kampala. Other forums for dissemination will include annual research meetings and forums virtually and in-person. If JoL is proven to be effective, the adapted manual will be shared with program developers, implementation staff, and key partners in order to facilitate scale up of implementation. REPSSI will also disseminate the adapted manual across countries of operation. Furthermore, results will be published in English in peer-reviewed journals for regional and global audiences.

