We acknowledge potential challenges that may emerge during the implementation and evaluation of the JoL program. One of these challenges includes operating during the COVID-19 pandemic. Good practice safety measures have been put in place to protect the health of staff and participants involved in the program and evaluation. Another challenge may involve operating during the wet season in Uganda, which may affect access and participation and will be monitored as part of program M&E. Additionally, we have tried to account for potential spillover effects by ensuring the selected Ranches are sufficiently geographically separated. We know that groups of participants will include community members who hold various roles in the community who may engage with program material differently; we will be carefully monitoring and working to minimize power dynamics within the groups. Implementation and evaluation staff will monitor emerging issues, and provide a constructive environment for participation.

The primary goal of JoL is to provide a sustainable solution to support the wellbeing of children and families living in Kiryandongo, Uganda. Following intervention delivery, it is hypothesized that participants will have improved self-care strategies and be better able to promote and improve child wellbeing. Overall, this study supports burgeoning literature about caregiver psychosocial support and child protection programs in humanitarian and low-resourced settings.

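### With one Ranch per arm, the 5% level and the 80% power hold only if the two Ranches would have changed alike and outcomes are independent within JoL groups; the plan states neither condition

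*Protocol article*

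**What the plan says.** Protocol article, Study design: "the treatment group will be conducted in one Ranch (a demarcated segment of the settlement) of Kiryandongo". The waitlist control has one other Ranch, geographically apart from the first. Outcomes are measured twice, at baseline and at endline. The Abstract gives the sizes as "intervention *n* = 600, control *n* = 600", and the design is called quasi-experimental throughout.

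Quantitative study design: the sample, "assuming 80% retention of an initial" 1200, leaves 960, which "is adequate for detecting an effect size of 11% with 80% power". The tool is R's power.prop.test, which compares two independent proportions. No ICC or design effect is given.

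Quantitative analysis: "The level of significance for all analyses will be set at 5" per cent. Individuals are classified by arm. The mixed models are described through subjects and time-points, and are meant to separate the effect of time from that of the programme.

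Discussion: the programme runs in groups, with staff "working to minimize power dynamics within the groups". Spillover is the only between-Ranch issue raised. Dissemination: "If JoL is proven to be effective", the adapted manual is shared to help scale-up.

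**The concern.** A before-and-after comparison removes stable differences between the Ranches. It does not remove change that is specific to one Ranch, such as a change in services or access that reaches one and not the other. With a single Ranch in each arm there are no degrees of freedom between Ranches within an arm, so the data cannot estimate the size of such change. No random effect or robust standard error in an analysis plan could supply it. Time can be separated from the programme only if it acts equally in both Ranches.

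Participants in the same JoL group also share sessions and facilitators, so their outcomes may be correlated at endline. The sample-size calculation allows for neither source.

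At stake is the primary conclusion on mental distress. An individual-level p-value below 0.05 could come from an ordinary difference in trend between two places and be read as evidence for JoL.

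**Working it through.** **Inputs from the document.** One Ranch per arm; 1200 × 0.8 = 960, or 480 per arm; 5% level (two-sided assumed); 80% power; an effect of 11%, not stated to be absolute or relative.

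**Inputs assumed, because the document gives none.** Within-person correlation 0.5; Ranch-by-time variance s of 0.1%, 0.5% or 1% of the Kessler-6 variance; JoL groups of 20 with 16 retained; group ICC 0.02 to 0.05, acting on the change and in the intervention arm only.

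**1. The plan's own 80%.** Take 11% as absolute, in the worst case of 44.5% against 55.5%. The required number per arm is

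[1.96·√(2·0.5·0.5) + 0.8416·√(2·0.445·0.555)]² / 0.11² = 323.2, so 324.

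With 480 per arm, power is 92.7%, so the stated 80% is not reproduced. The slack is 480/324 = 1.48. Read as relative, 80% is reproduced only at an unstated baseline of about 74.8% (falling to 66.5%) or 71.1% (rising to 78.9%), and then there is no slack.

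**2. Ranch-by-time variation and the 5% level.** In SD units, under independence, the variance of the difference in change is 2·2(1 − 0.5)/480 = 0.00417. The SE is 0.0645, and the detectable effect is 2.80 × 0.0645 = 0.18 SD. Each of the four Ranch-by-time cells adds its own s, so the true variance is 0.00417 + 4s. The real error is 2·[1 − Φ(1.96/ratio)], where ratio is true SE over naive SE.

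| s | True variance | SE ratio | Real error of nominal 5% test | Detectable effect |
|---|---|---|---|---|
| 0 | 0.00417 | 1.00 | 5% | 0.18 SD |
| 0.001 | 0.00817 | 1.40 | 16% | 0.25 SD |
| 0.005 | 0.02417 | 2.41 | 42% | 0.44 SD |
| 0.01 | 0.04417 | 3.26 | 55% | 0.59 SD |

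The detectable effects suppose that s is known, which it is not.

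A simpler set-up gives smaller figures in the same direction. It compares the Ranches once, with design effect 1 + 479·ICC. ICCs of 0.001, 0.005 and 0.01 give design effects of 1.48, 3.40 and 5.79, and errors of 10.7%, 28.7% and 41.5%.

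**3. JoL-group clustering alone.** The design effect in the intervention arm is 1 + 15·ICC, which is 1.30 or 1.75. Averaged with 1 for control, it is 1.15 or 1.375, so the SE ratio is 1.07 or 1.17. The naive SE is too small by 1 − 1/1.07 = 7% or 1 − 1/1.17 = 15%. The real error is 6.8% or 9.5%.

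**4. Effect on power.** Power is recalculated with 480 divided by the design effect. The relative column uses 74.8% falling to 66.5%.

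| Source | Design effect | Absolute 11 points | Relative 11% |
|---|---|---|---|
| None | 1 | 93% | 80% |
| Group, ICC 0.02 | 1.15 | 89% | 74% |
| Group, ICC 0.05 | 1.375 | 83% | 67% |
| Ranch, ICC 0.001 | 1.48 | 80% | 63% |
| Ranch, ICC 0.005 | 3.40 | 46% | 33% |
| Ranch, ICC 0.01 | 5.79 | 29% | 21% |

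**The case against.** **Disclosure.** The design is openly quasi-experimental, and separate Ranches were chosen for a good reason: to limit contamination. A concurrent control also removes any effect of the rains or COVID-19 that falls on both Ranches alike. This stands. But disclosing that allocation was not randomised does not make the 5% level valid, and equal trends in the two Ranches are assumed without being stated.

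**Power.** A reader might infer that the 80% power has been shown to fail. The document does not support that. On the absolute reading, power stays above 80% under the group clustering assumed here, and is still about 80% at a Ranch ICC of 0.001.

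**Group and household terms.** A reader might infer that the analysis will ignore group clustering because the article names no level above the participant. A condensed article need not list random effects, and generalized mixed models can hold such terms. What remains is that the sample-size method assumes independence. Household clustering is only a possibility: the eligibility rules do not exclude several adults from one household, but nothing says that they will be enrolled.

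**Scale-up.** A reader might infer that scale-up hangs on one p-value. The Dissemination section does not say so, and the analysis section speaks of a meaningful difference. The wording leaves the standard of proof open.

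**Size.** The error rates rest on assumed variances, and the two set-ups in the working differ. They show direction and plausible scale, not an estimate.

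**Conclusion.** The concern holds in conditional form. Ranch-by-time change is fully confounded with JoL, and this follows from the design, whatever a fuller analysis plan contains. The nominal 5% is valid only if that variation is zero and outcomes are independent within groups; any positive correlation raises it. The sizes are about 16%, 42% or 55% for Ranch-by-time variance of 0.1%, 0.5% or 1% (480 per Ranch, within-person correlation 0.5), and about 7% to 10% from JoL groups alone (16 retained, ICC 0.02 to 0.05, intervention arm only). The 80% power is not supported as stated, because it depends on an undefined 11% and on independence. It has not been shown to be wrong.

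**What to change.** 1. State the 5% level and the 80% power as conditional on no Ranch-by-time variation and on independence within JoL groups. Restate power over a range of ICCs, saying whether 11% is absolute or relative and from what baseline.
2. Record JoL group ID. Fit a partially nested group effect that acts at endline (group-by-time), in the intervention Ranch only; a group intercept constant over time would largely cancel from the change. Add a household term only if several adults per household are enrolled.
3. Pre-specify a sensitivity analysis that recomputes the confidence interval with assumed Ranch-by-time variance of 0.1%, 0.5% and 1% of the total.
4. Report the result as a difference in change between two Ranches, conditional on equal trends. Do not treat effectiveness as proven on the individual-level p-value alone.

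Item 2 deals only with the group-level part. Items 1, 3 and 4 do not remove the Ranch confounding; they make the conclusion match what two Ranches can show.

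**Cost.** Wording, one ID field (plus household ID if needed) and one sensitivity table; no more participants. The downside is wider intervals and a less favourable stated power. Under the assumptions above, the 95% half-width grows from 1.96 × 0.0645 = 0.13 SD by the SE ratios 1.40, 2.41 and 3.26, to about 0.18, 0.30 and 0.41 SD.

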**Fig. 1 Fig1:**
[figure not shown]
Study flow chart

### Quantitative study design

Every community member (intervention and wait-list control) invited to participate in JoL will also be invited to participate in the evaluation study. To ensure sufficient power, we conducted a sample size calculation for our primary outcome measure – mental distress, measured through the Kessler 6. The proposed sample size (*n* = 960; assuming 80% retention of an initial *n* = 1200) is adequate for detecting an effect size of 11% with 80% power. R (base library, command power.prop.test) was used to conduct the power analysis. We intend to maximize our sample in order to be able to explore potential differences between males and females, and also to be able to look at per-protocol (those who attend > 75% of sessions) versus intent-to-treat analyses.

### Recruitment and population characteristics

Participant recruitment will be conducted in collaboration with the staff of the implementing organization and their community partners. Inclusion criteria for participation in JoL is any person (men and women) ages 18 and over who lives with a child under 18 years old or has caregiving responsibilities for someone under the age of 18. Participants can be refugees or Ugandan nationals living in the study location, they do not need to meet any criteria for adverse mental health, including stress or mild mental illness. Additionally, individuals who have experienced an adverse mental health event are not excluded from the study. Exclusion criteria for the intervention includes anyone aged 17 and under and anyone who is not able to consent to participate.

